### Recruitment {15}

The recruitment strategy for this study involves a multifaceted approach. Primarily, participants will be recruited via the Memory Clinic of the MUMC + , targeting patients diagnosed with (a)MCI or mild dementia, along with their (informal) caregivers. Treating doctors at the Memory Clinic will assess eligibility using an exclusion checklist provided by the study investigators. While the study is designated as a mono-centre, collaboration with regional hospitals in the Netherlands and Belgium, such as Zuyderland Medical Centre, will be instrumental in extending outreach. Treating doctors at these regional hospitals will be informed about the study, allowing them to provide eligible patients with the patient information sheet. Additionally, recruitment efforts will extend to online platforms and relevant websites including those of Alzheimer Nederland (www.alzheimer-nederland.nl), Alzheimer Centrum Limburg (www.alzheimercentrumlimburg.nl), and Hersenstichting (www.hersenstichting.nl). Thematic newsletters and social media channels will also be leveraged. Prospective participants expressing interest will be guided by the researcher provided with the patient information sheet and granted a minimum of 7 days for thoughtful consideration. To validate the specific diagnosis, patients will be requested to bring the confirmation letter of their diagnosis from their medical specialist [28] to the screening visit, ensuring precision in participant selection.

## Assignment of interventions: allocation

### Sequence generation {16a}

Randomization and treatment allocation will be performed by an independent researcher, as the trial will be conducted in a randomized double-blind manner. The allocation sequence will be generated by an independent researcher using a computerized random number generator (https://commentpicker.com/random-number-generator.php). The randomization will be a block randomization of 12 participants (randomization within these blocks). The randomization list will be sent to the GMP-certified manufacturer and the trial pharmacy of the MUMC + .

### Concealment mechanism {16b}

The independent researcher will be responsible for conveying the randomization list to the GMP-certified manufacturer. Employing a coding system, the manufacturer will assign codes to the various treatments, facilitating the blinding of the study medication. The manufacturer will then proceed to prepare coded jars containing the study medication, adhering to the predetermined dosage levels. The manufactured and coded study medication will undergo a comprehensive quality control process to ensure adherence to regulatory standards. Subsequently, the coded jars will be shipped to the trial pharmacy of the hospital. A researcher of the study will be able to pick up the study medication based on a prescription from a medical doctor.

### Implementation {16c}

The randomization list will be sent to the manufacturer and the trial pharmacy. Subsequently, the researcher will oversee the enrollment of participants, who will be systematically allocated to specific interventions based on their designated participant numbers. This method ensures an unbiased and randomized assignment, contributing to the scientific rigour and validity of the study design.

## Assignment of interventions: blinding

### Who will be blinded {17a}

Trial participants, their (informal) caregivers, care providers, and the research team will remain blinded throughout the research. Only the independent researcher taking care of the randomization and concealed treatment allocation sequencing, the manufacturer that will produce the study medication, and the MUMC + trial pharmacy will know the participant’s treatment allocation. The research physician will be employed as a backup to unblind in case the independent researcher is not available in case of urgency. The study medication will be produced in identically appearing capsules in identically appearing jars, with neutral identification capsule jar labelling, such as 01(subject)_1(jar) for the first 12 weeks and 01(subject)_2(jar) for the subsequent 12 weeks.

### Procedure for unblinding if needed {17b}

In the case of unblinding, the research team has appointed an independent researcher to unblind. In situations where the designated independent researcher is unavailable, the research physician associated with the study is authorized to perform the unblinding process. Unblinding is a carefully regulated procedure and is only permissible under specific circumstances, particularly in emergencies such as (S)AEs, where a care provider requires knowledge of the administered dosage of the study medication.

## Data collection and management

### Plans for assessment and collection of outcomes {18a}

#### Verbal learning task (VLT)

In this study, the Dutch 15-VLT of Brand and Jolles (1985) serves as the primary tool for evaluating episodic memory [29]. This test entails a sequence of 15 Dutch monosyllabic words, presented for 1 s each, with an inter-stimulus interval of 1 s. Participants undergo five consecutive trials, with each trial culminating in a free recall of the presented words. The sum of the five recall trials results in the immediate recall score. Following a 20-min delay, during which no verbal memory tasks are performed, the participants are unexpectedly prompted to recall the previously learned words (delayed recall). Subsequently, a recognition test is administered, involving the discrimination of 15 stimulus words from 15 distractor words in a yes/no format. To mitigate learning effects, five Dutch parallel versions of the 15-VLT are utilized. Key dependent measures are the total number of correctly remembered words in the five learning trials (total immediate recall score), reflecting short-term verbal declarative memory, learning, and retrieval. Furthermore, the delayed recall score assesses the number of correctly recalled words after the 20-min interval. The amount of correctly recognized words assesses long-term verbal memory retrieval. The 15-VLT has well-established normative data derived from a cohort of over 1800 healthy individuals in the Dutch population [27].

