Our secondary objectives encompass a comprehensive exploration of diverse cognitive domains. Included cognitive domains are as follows: mental speed/attention and executive functioning (Letter Digit Substitution Test (LDST) and Trail Making Test (TMT)), spatial memory (Spatial Pattern Separation Task), language (Alzheimer’s Disease Assessment Scale-Cognitive Subscale (ADAS-Cog), and the Shortened Boston Naming Test-15 (BNT-15)) and orientation (Mini-Mental State Examination (MMSE)) will be measured as well. In addition to cognitive assessments, we aim to gauge participants’ quality of life (Quality of Life AD (QoL-AD), EuroQol-5 Dimensions (EQ-5D)), psychological well-being (Hospital Anxiety Depression Scale; HADS), neuropsychiatric symptoms (Neuropsychiatric Inventory; NPI), and daily functioning (Alzheimer’s Disease Cooperative Activities of Daily Living Scale; ADCS-ADL). This multifaceted approach aims to illuminate the intricate interplay between cognition, quality of life, mood, and emotion. Outcome measures include a decrease in the reaction time (RT) in the LDST and TMT, as well as a decrease in errors in the LDST. Anticipated improvements encompass an increased total recognition score on the 15-VLT and an increased accuracy in all identified pattern completion scores of the pattern separation memory task. Total scores on the MMSE and ADAS-cog are expected to improve, as well as increased scores in well-being and quality of life, as indicated by the participant and the (informal) caregiver questionnaires. Furthermore, tau measurements from tear fluid samples will be assessed, as we speculate a potential positive impact of roflumilast on phosphorylated tau (pTau) concentrations [22]. Lastly, we will monitor the conversion from (a)MCI to dementia.

Three primary hypotheses have been formulated:The administration of 50 μg roflumilast over a chronic treatment period of 24 weeks, compared to placebo, is anticipated to improve episodic memory in participants with aMCI or mild AD dementia;The administration of 100 μg roflumilast over a chronic treatment period of 24 weeks, compared to placebo, is anticipated to improve episodic memory in participants with aMCI or mild AD dementia;The administration of 50 μg roflumilast over a chronic treatment period of 24 weeks, compared to 100 μg roflumilast, is anticipated to have comparable effects on episodic memory in participants with aMCI or mild AD dementia.

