### Outcomes {12}

#### Primary study parameter

The primary outcome measure is verbal memory using the 15-VLT [27]. The 15-VLT is chosen as our primary outcome because it assesses episodic memory—a cognitive domain linked with hippocampal function [18]. Considering the evidence of high PDE4 expression in the hippocampus [19] and observable atrophy in the medial temporal lobe regions of individuals diagnosed with MCI [17, 20]. Accordingly, a larger effect size for cognitive functions and tasks related to this brain area is expected. Variables include correct immediate recall on trial 1 to trial 5, correct total immediate recall (sum of all 5 trials), and correct delayed recall. Change from baseline to acute effects, change from baseline to 3 months, change from baseline to 6 months, and 6 months to follow-up will be statistically analysed.

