#### Secondary study parameters

Our secondary objectives include a comprehensive evaluation of various cognitive domains, extending beyond the primary focus on verbal memory. The LDST serves as a metric for assessing visual scanning, mental flexibility, sustained attention, psychomotor speed, and speed of information processing. The LDST outcomes include the total number of correct written items after 90 s, and the total number of correct items read after 90 s. The TMT measures visual attention (Part A) executive functioning and mental flexibility (Part B). The TMT outcome is the time (in seconds) required to complete each part individually (Part A and Part B). Spatial memory is measured by the spatial pattern separation task, evaluating participants’ accuracy in identifying the position of objects on a computer screen. The ADAS-Cog will be used as it measures language and memory in general. Subtests within the ADAS-Cog encompass naming objects and fingers, following commands, constructional praxis, ideational praxis, orientation, remembering test directions, spoken language, comprehension, and word-finding difficulty. The total score of the subtests is utilized as the ADAS-Cog. The word recall task and the word recognition task have been removed from the task, to avoid interference with our primary outcome measure (15-VLT). The 15-VLT recognition task is part of the secondary outcomes. The MMSE serves as a screening tool for general cognitive impairment, with the total score acting as the MMSE outcome. Confrontational naming is assessed through the Shortened BNT-15, with the total score derived from correctly named items, either spontaneously or after semantic cues.

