### Statistical methods

#### Statistical methods for primary and secondary outcomes {20a}

Descriptive statistics for continuous parameters will include sample sizes, means and standard errors of the dependent variables, and covariates for each distinct level combination of factors. For categorical data, summary tables will present counts and percentages. Statistical summaries will be presented by treatment, sequence, or period. The repeated measures, namely the outcome variables of the cognitive assessments and the subjective well-being-related scales, will be analysed using mixed models. The between-subject factor will be the treatment group (three levels: placebo, 50 μg roflumilast, and 100 μg roflumilast). The scores of each task will be entered as the within-subject factor, as well as time (T1, i.e. acute, T2, i.e. 12 weeks, T3, i.e. 24 weeks, T4, i.e. 2-week follow-up). An additional interaction term between the treatment group and time is included to determine whether the different treatment groups will lead to different trajectories over time. Subject covariates included will be sex, age, and education. Additionally, at the end of the study, we will ask each participant which intervention arm they think they have received (placebo, 50 mcg roflumilast, or 100 mcg roflumilast). Because of exclusion and inclusion criteria related to the patient recruitment of the study, the population recruited will be homogenous. Note that groups will not be able to be matched because of the applied randomization block strategy. The significance level will be set at *a* = 0.05.

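### As worded, the 15-VLT recognition score reads as hits only and does not use the distractor answers; a score that uses both would be a minor improvement to one secondary outcome

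*Protocol article*

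**What the plan says.** The section on the verbal learning task, under Plans for assessment and collection of outcomes {18a}, describes the recognition test as "involving the discrimination of 15 stimulus words from 15 distractor words in a yes/no format". It then lists the dependent measures: the total over the five learning trials, the delayed recall count, and recognition. For recognition it says: "The amount of correctly recognized words assesses long-term verbal memory retrieval".

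Objectives {7} gives the expected direction: "Anticipated improvements encompass an increased total recognition score on the 15-VLT". The composition and maximum of that total are not given.

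Secondary study parameters sets the status of the measure: "The 15-VLT recognition task is part of the secondary outcomes". All secondary outcomes are to be analysed as changes from baseline to the acute, 3-month and 6-month visits, and from 6 months to follow-up.

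The primary variables are free recall only: "Variables include correct immediate recall on trial 1 to trial 5, correct total immediate recall (sum of all 5 trials), and correct delayed recall".

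The article does not mention false alarms, correct rejections or a discrimination index. It also does not say that distractor answers are left out of the score.

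**The concern.** A yes/no recognition test yields two numbers: 'yes' answers to studied words (hits) and 'yes' answers to distractors (false alarms). Memory shows in the difference between them. Hits alone also rise when a person simply becomes more willing to say 'yes'.

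The sentence that defines the measure speaks of words correctly recognised. Only a studied word can be recognised, since a distractor is correctly rejected. The wording also runs parallel to the two recall measures before it, which count studied words. The natural reading is therefore hits, which does not match a test described as discrimination.

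The stake is a secondary outcome with a stated direction. If it is scored as hits, any effect of treatment on response style would look like an effect on memory. Even without such an effect, half of the answers would go unused.

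**Working it through.** The protocol gives no sample size, power or error figure for recognition, so there is no figure of the plan to reproduce. The check has three parts.

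**1. Counting (no assumptions).** Let H be hits of 15 and F false alarms of 15.

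- All 'yes': H = 15, F = 15. Hits = 15/15, the maximum. Correct of 30 = H + (15 − F) = 15, which is chance. H − F = 0.
- A participant with H = 11 and F = 0: hits = 11, below the all-'yes' responder. Correct of 30 = 26. H − F = 11.
- Correct of 30 = (H − F) + 15, so the two scores differ by a constant and give identical tests.

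**2. Effect of response style at fixed memory (assumed values).** The equal-variance signal-detection model has hit rate Φ(d′/2 − c) and false-alarm rate Φ(−d′/2 − c), each times 15. The documents give no d′ or c. With d′ = 1:

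| Criterion c | Hits | False alarms | Hits − false alarms |
|---|---|---|---|
| +0.5 | 7.50 | 2.38 | 5.12 |
| 0 | 10.37 | 4.63 | 5.74 |
| −0.5 | 12.62 | 7.50 | 5.12 |

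From c = +0.5 to −0.5, hits rise by 12.62 − 7.50 = 5.1 words with memory unchanged, while hits minus false alarms moves by at most 0.62. For d′ from 0.5 to 2.0, the same shift adds 5.6 words (6.02 to 11.60) down to 3.6 words (10.37 to 14.00).

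**3. Simulated two-arm comparisons (assumed values).** Mean d′ is 1 (SD 0.5), mean criterion 0 (SD 0.4), 24 per arm (the group size before the dropout allowance, Sample size {14}), two-sided 0.05, t-tests, 20,000 runs.

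| Scenario | Hits | Hits − false alarms |
|---|---|---|
| No memory effect, no shift (rejection rate) | about 5% | about 5% |
| No memory effect, criterion shift of 0.3 in one arm, single visit | about 40% | about 5% |
| True gain of 0.4 in d′, no shift, single visit | about 21% | about 47% |
| True gain of 0.4 in d′, no shift, change from baseline, each person's criterion the same at both visits | about 26% | about 46% |

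The shift of 0.3 produces a false difference of about 1.4 words. With criterion SD from 0.3 to 0.5, the 40% runs from about 48% down to about 32%.

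To find the source of the power gap, set the criterion SD to zero. Single-visit power is then about 35% against about 50%, a gap of 15 points. The gap with criterion SD 0.4 is 47 − 21 = 26 points. So more than half of it comes from scoring 15 answers rather than 30, and the rest from personal variation in response style.

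**The case against.** **The text does not state that false alarms are ignored.** A reader might infer that the plan has fixed a hits-only score. The documents do not support that as fact. The test is described as discrimination, the Objectives speak of a total recognition score, and no maximum is given. If the total is correct answers out of 30, an all-'yes' responder scores at chance and the consequences above do not follow. This stands, and the point must be put as 'as worded'. It does not remove the point: on that reading, the sentence that defines the measure misdescribes the score and needs the same edit.

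**Scoring detail belongs in the full protocol, the test manual or the analysis plan.** That is fair for detail the article leaves out. Here the article does state the measure, and its statement does not match the test it describes.

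**Bias needs a mechanism the protocol does not contain.** The trial is double-blind with identical capsules. A reader might infer that hits-only scoring inflates the false-positive rate to 40%. It does so only if treatment shifts response style by the assumed amount in one arm, and nothing in the article suggests such a shift. Without one, the hits-only test is valid. This stands. Blinding does not, however, rule out a pharmacological effect on response style, and analysing change from baseline would not remove one.

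**The loss of power is not simply due to guessing and depends on the analysis.** A reader might infer that variation in guessing alone more than halves power. The change-from-baseline result (26% against 46%) and the zero-variation result (35% against about 50%) do not support that. The planned mixed model over several visits was not simulated. This stands; what remains is a clear advantage in sensitivity whose exact size depends on assumptions.

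**Conclusion.** The concern holds in a limited form. As worded, the recognition measure reads as hits only, and no section says that distractor answers count. Under that reading, the score confounds memory with willingness to say 'yes', and 30 'yes' answers earn the maximum; this follows from counting alone.

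For the comparison of arms, the consequence is conditional. Bias arises only if treatment shifts response style. Otherwise the test keeps its level, and the cost is lower sensitivity, roughly half the power in the scenarios examined. All of these percentages rest on assumed signal-detection values, because the documents give none.

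Recognition is one of many secondary outcomes. The primary free-recall variables and the sample size do not depend on it. This is a minor improvement.

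**What to change.** In Secondary study parameters and in the verbal learning task section, define the tested 15-VLT recognition score as hits minus false alarms (range −15 to 15), and note that it equals correct answers out of 30 minus 15. Report hits and false alarms separately by arm as description only. Settle this before unblinding, so that the score is not chosen after the results are seen.

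The cost is one sentence. The yes/no format already collects the distractor answers, so no procedure changes. If correct answers out of 30 were intended all along, the test result does not change. The one small downside is less direct comparability with sources that report hits only, and the separate report of hits largely covers that.

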#### Mini-mental state examination (MMSE)

The Dutch standardized MMSE is a commonly used screening instrument for cognitive function [30] consisting of 13 items that evaluate the domains of orientation, registration (immediate memory), short-term memory, attention, and language functioning. The maximum score is 30. The outcome measure of the MMSE is the total score. The instrument demonstrates commendable test–retest reliability and exhibits acceptable sensitivity and specificity, rendering it proficient in detecting mild to moderate stages of dementia [31].

#### Trail making test (TMT)

The TMT is a neuropsychological test designed to measure visual attention and task-switching capabilities [32]. The TMT provides information about visual search speed, scanning efficiency, processing speed, mental flexibility, and executive functioning. Compromising Part A and Part B, Part A instructs participants to connect a set of 25 circles—including the numbers 1 to 25—in sequential order as quickly as possible while still maintaining accuracy. Part A is used to primarily evaluate cognitive processing speed. Meanwhile, Part B evaluates executive functioning, specifically mental flexibility, as participants connect numbers and letters alternately (1, A, 2, B, etc.). The primary performance metric is the time in seconds taken to complete each part of the test individually, with the assumption that any errors made will be reflected in the completion time.

#### Letter digit substitution test [33]

The LDST [34], an adapted version of earlier substitution tests such as the Digit Symbol Substitution Test, serves as a tool for assessing information processing speed. Participants are presented with a test sheet featuring a key on the top, associating numbers 1 to 9 with different letters. The test items, displayed beneath the key, require participants to replace randomized letters with the corresponding digit indicated by the key. To familiarize participants with the task, initial 10 items serve as a practice round. Following these, participants are instructed to complete the remaining items as quickly as possible, by writing them down in the first round and naming them out loud in the second round. The dependent variables are the number of correct substitutions 90 s for both writing and naming rounds.

#### Boston naming test, 15 items (BNT-15)

The BNT-15 [35], as outlined by Kaplan et al., serves as an instrument for evaluating language performance. Participants are tasked with naming a series of objects within a stipulated timeframe of 20 s. The test compromises five easy, five moderately difficult, and five difficult items. The total score is derived from items correctly named spontaneously, plus additional items named correctly after semantic cues.

#### Alzheimer’s disease assessment scale – cognitive subscale (ADAS-Cog)

Developed in a collaborated effort in the 1980s, the ADAS-Cog is seen as a widely used cognitive assessment in clinical trials to measure the efficacy of pharmaceutical interventions regarding dementia [36, 37]. The ADAS-Cog includes participant-completed and observer-based assessments: summarized, word recall, naming objects and fingers, commands, constructional praxis, ideational praxis, orientation, word recognition, and language. Language includes the assessment of quality of speech, as well as comprehension of spoken language. For our study, we have removed the word recall and word recognition because of interference with the 15-VLT. It is important to mention that some significant variance in administration and thus reliability has been found [36]. Subsequently, it is imperative to ensure that personnel involved in the administration of ADAS-Cog undergo thorough training in adherence to standardized operating procedures.

